**Conclusions:**

This study aims to evaluate the efficacy and safety of *tuina* therapy in the treatment of adolescents with myopia. We hypothesize that the therapeutic effect of *tuina* therapy is noninferior to that of tropicamide eye drops, with the additional advantages of fewer side effects and stable long-term efficacy, thereby providing reliable evidence and support for the application of *tuina* therapy in the management of myopia in adolescents.

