### Objectives

This study aims to conduct a high-quality randomized controlled trial to objectively evaluate the efficacy and safety of selective spinal *tuina* manipulation therapy in the treatment of childhood myopia. We hypothesize that selective spinal manipulation therapy can improve vision in children with myopia and is safer than drug therapy, with no side effects and more stable long-term efficacy.

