## Methods

### Study Design

This study is designed as a multicenter randomized controlled noninferiority trial to be conducted from June 2025 to October 2026. We plan to recruit 62 participants from 4 hospitals in Yunnan Province. Eligible participants will be randomly assigned in a 1:1 ratio to the *tuina* experimental group and the positive drug control group (tropicamide eye drops). Each participant will undergo an 8-week treatment period followed by a 2-week follow-up. Baseline information and outcomes will be assessed at baseline, at the completion of weeks 4 and 8 of treatment, and at the end of the 10-week follow-up (Figure 1). This trial adheres to the guidelines of the SPIRIT (Standard Protocol Items: Recommendations for Interventional Trials).

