### Data Analysis

All data will be analyzed using SPSS version 28.0 and GraphPad Prism version 10.3.1 statistical software. For normally distributed data, results will be described as mean (SD) and analyzed using the *t* test. For nonnormally distributed data, results will be described as median (IQR) and analyzed using the Wilcoxon rank sum test for within-group comparisons and the Mann-Whitney *U* test for between-group comparisons. A 2-sided *P* value of .05 will be considered statistically significant. Missing data will be handled using expectation maximization, last observation carried forward, or listwise deletion.

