## Results

As of December 2025, 29 participants have been enrolled, with 16 allocated to the *tuina* experimental group and 13 allocated to the drug-positive control group. The current data indicate that *tuina* therapy is helpful in enhancing UCVA and improving AL of eyes, with no AEs reported, suggesting that *tuina* therapy is an effective alternative treatment. The enrollment process will continue until October 2026. We will submit the final manuscript before December 2026, following which we will disseminate the final results in accordance with the CONSORT checklist.

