
### Innovations and Limitations

It should be noted that this study also has certain limitations: First, given that *tuina* therapy relies on the proficient mastery of techniques and acupoints by the practitioner, it is difficult to implement a blinded design. As a form of physical contact between the practitioner and the patient, *tuina* therapy, whether or not it targets specific acupoints, inevitably stimulates the skin, muscles, and peripheral nerves. Therefore, it is also challenging to blind the patients. Consequently, a sham *tuina* group was not included. However, relatively standardized operational protocols and procedures have been established, and all participating practitioners must strictly adhere to them in an effort to minimize such differences. Nevertheless, completely eliminating such differences is challenging. If subsequent analyses reveal that these differences significantly impact the results, they will be considered incorporating them into our analytical models to ensure the accuracy and reliability of our findings. Second, due to financial and human resource constraints, this study does not conduct a multicenter trial involving the entire country. Future work will aim to expand the scope of the study.

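### Within-group significance tests share the .05 rule with the between-group tests, and nothing stops them from supporting the hypothesis that tuina improves vision

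*Protocol article*

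**What the plan says.** The protocol article words its efficacy question in two ways.

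- **Absolute.** Objectives: "We hypothesize that selective spinal manipulation therapy can improve vision in children with myopia and is safer than drug therapy". The part about vision names no comparator.
- **Comparative.** The Conclusions of the abstract: "We hypothesize that the therapeutic effect of *tuina* therapy is noninferior to that of tropicamide eye drops". Study Design agrees: "This study is designed as a multicenter randomized controlled noninferiority trial". Expected Findings also frames efficacy relative to drug therapy.

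Under Data Analysis, non-normal data are to be "analyzed using the Wilcoxon rank sum test for within-group comparisons", with Mann-Whitney U between groups. For normal data it names a t test without saying whether it is paired or independent. One two-sided .05 threshold covers everything, and neither comparison is named as the one that carries the efficacy conclusion.

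The only comparator is tropicamide. Innovations and Limitations, after explaining why blinding patients is difficult, adds: "Consequently, a sham *tuina* group was not included". Outcomes are measured at baseline and at weeks 4, 8 and 10.

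The Results section, with 29 children enrolled, says that "therapy is helpful in enhancing UCVA and improving AL of eyes" and quotes no between-group contrast.

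**The concern.** No randomised comparison in this trial sets tuina against no treatment or sham. The within-group test is therefore the only listed test that bears directly on the absolute hypothesis in Objectives. Its null is that scores do not change between visits, which is not the same as tuina having no effect. The two nulls differ whenever children would score differently at follow-up for reasons unrelated to treatment.

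Uncorrected visual acuity (UCVA) is open to this. It is a chart reading that depends on the child's response, it is taken four times, and the child knows the treatment. Practice or expectation could raise the score with no treatment effect. As the plan is worded, a significant before-after P value in the tuina arm could then be reported as evidence of efficacy, whatever the randomised comparison shows.

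**Working it through.** **1. The plan's own figure.** Inputs from Sample Size: effect size 0.8 (read as a standardised mean difference), two-sided alpha .05, power 80%, 1:1 allocation. A two-sample t test needs 25.52 per group, rounded up to 26, so 52 in total; power at 26 per group is 80.7%. This reproduces the stated 52. The stated 62 (31 per group) follows as 52 × 1.2 = 62.4, rounded down. The trial was therefore sized for a between-group difference. The 26 and 31 per arm are used below.

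**2. What each test asks.** Let s be the mean shift that would occur without treatment, and let τ_T and τ_D be the effects of tuina and of the drug.

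- Within the tuina arm, the null is s + τ_T = 0.
- Between arms, with the same s in both, the null is τ_T − τ_D = 0.
- The absolute hypothesis in Objectives is that τ_T is favourable.

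The within-arm test can reject with τ_T = 0 as soon as s ≠ 0. The between-arm test is free of s but speaks only to tuina relative to tropicamide.

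**3. Size of the problem for a paired test.** Write d for s divided by the SD of the change score. The article gives neither quantity, so d is an assumed range. With no treatment effect, the rejection rate is P(|T| > t(0.975, n−1)), where T is noncentral t with n−1 degrees of freedom and noncentrality d√n. For n = 26 and d = 0.2 the noncentrality is 0.2 × 5.10 = 1.02; for d = 0.5 it is 2.55.

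**4. Comparison with the other tests.** The last two columns are simulated: 4,000 runs per setting, 26 per arm, the same shift in both arms, no treatment effect, and an assumed baseline-to-follow-up correlation of 0.8.

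| d (assumed) | Paired t, n = 26 | Paired t, n = 31 | Between-group t on change | Rank-sum applied to paired data |
|---|---|---|---|---|
| 0 | 5.0% | 5.0% | 4.7% | 0.1% |
| 0.2 | 16.5% | 19.0% | 5.3% | 0.3% |
| 0.3 | 31.3% | 36.6% | 4.5% | 1% |
| 0.4 | 50.0% | 57.8% | not run | not run |
| 0.5 | 68.8% | 76.8% | 4.9% | 6% |
| 0.8 | 97.5% | 99.1% | 4.7% | 36% |

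For a favourable shift of 0.2 SD or more, nearly all the paired rejections are in the favourable direction (16.4 of the 16.5 percentage points at d = 0.2, n = 26). A Wilcoxon signed-rank test in the same simulation gave 17.2%, 31.2% and 67.1% at d = 0.2, 0.3 and 0.5, close to the paired t test.

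**5. Why the named test behaves differently.** The rank-sum test is an independent-samples test, equivalent to Mann-Whitney. With correlation 0.8, the variance of a paired difference is 2(1 − 0.8) = 0.4 times the outcome variance, but an unpaired test works as if it were 2 times. Its standard error is too large by √(2/0.4) = 2.24, which makes it conservative. If the test name is corrected to the signed-rank test and nothing else changes, the rejection rates move to the paired columns.

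**The case against.** The strongest reply is that no sentence gives the decision to the within-group test. Sample Size targets between-group differences, Study Design names a noninferiority trial, and the abstract and Expected Findings frame efficacy against the drug. Which comparison carries the conclusion may be fixed in a fuller document that is not shown. This stands as far as it goes: a reader might infer that before-after tests decide efficacy, and the article does not say so. It does not dispose of the point, because the absolute hypothesis and the within-group tests at .05 are both in the text, and together they permit that use.

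Four further inferences are tempting and not supported.

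- **Growth.** Axial elongation lengthens the eye and tends to worsen UCVA and refraction. It works against a false finding of benefit.
- **Regression to the mean in UCVA.** Entry is by dioptres (mild to moderate myopia), and no UCVA threshold is stated. The refractive range has a limit at each end, and these pull in opposite directions.
- **The Results statement as a within-group finding.** It quotes no test, P value or contrast. It shows absolute wording already in use, not how it was reached.
- **The 17% to 77% as the plan's actual error rate.** These figures need a paired test and an assumed drift. The rank-sum test as named gives about 0.3% to 6% over the same range.

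It is also fair to say that Randomization and Blinding provides for blinded outcome assessors. That limits assessor bias, but it does not remove practice or expectation in the child who reads the chart.

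**Conclusion.** The point holds in a limited form. The article states an absolute hypothesis, plans within-group significance tests under the same .05 rule as the randomised comparison, has no sham or untreated arm, and does not confine efficacy conclusions to the between-group contrast. A shift in UCVA from retesting or expectation could therefore be reported as a tuina effect.

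Its size depends on assumptions. With a paired test and a non-treatment shift of 0.2 to 0.5 SD of the change score, the within-arm test rejects about 17% to 69% of the time at n = 26 and 19% to 77% at n = 31, against a nominal 5%. The between-group test stays near 5% only if the shift is the same in both arms. Expectation could differ between hands-on sessions and eye drops in an open-label trial, and the randomised contrast would not remove that difference. The documents give no drift, SD of change or correlation, so these figures show how large the problem could be and do not estimate it.

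**What to change.** In Data Analysis, state that within-group changes are descriptive (mean or median change with a 95% confidence interval, no efficacy claim). State also that efficacy conclusions on UCVA, axial length, spherical equivalent and amplitude of accommodation rest on the randomised between-group difference, read as the noninferiority comparison named in the abstract and Study Design. The margin for that comparison is a separate matter, but the reading depends on one being fixed.

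Reword the efficacy hypothesis in Objectives to the same comparative question. Correct the name of the within-group test at the same time if any such test is kept; correcting the name alone would remove the conservatism and leave the inferential problem in place.

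The cost is wording only. No new data or visits are needed, and recruitment is still open. The trial gives up an absolute claim of improved vision based on before-after P values.

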### Sample Size

Using G*Power software to calculate the sample size, based on the preliminary pilot study results, the expected efficacy rate in the manipulation treatment group is above 80% (*P*<.05). Therefore, we set an expected effect size of 0.8. To detect between-group differences with 80% statistical power (*β*=.20), we choose a 2-tailed α level of .05. With an allocation ratio of 1:1, the required sample size was 52 participants (26 per group). Considering a 20% expected dropout rate, the final sample size was set at 62 participants (31 per group).

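### The rank test named for within-group comparisons is an independent-samples test and should be the signed-rank test; baseline adjustment between groups would be a free gain in precision

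*Protocol article*

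**What the plan says.** The Data Analysis section of the protocol article splits the methods by normality.

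- Normal data: "results will be described as mean (SD) and analyzed using the *t* test". It does not say whether the test is paired or unpaired, or whether follow-up values or changes are compared.
- Non-normal data: "analyzed using the Wilcoxon rank sum test for within-group comparisons" and "the Mann-Whitney *U* test for between-group comparisons".
- Threshold: "A 2-sided *P* value of .05 will be considered statistically significant".

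No covariate is named. Study Design and Data Management and Quality Control show that each child is measured four times: at baseline and at weeks 4, 8 and 10. Study Design also calls this a noninferiority trial in 4 hospitals.

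The only mention of a model is under Innovations and Limitations, about differences between practitioners: "If subsequent analyses reveal that these differences significantly impact the results, they will be considered incorporating them into our analytical models".

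**The concern.** The rank sum test and the Mann-Whitney U test are one procedure for two independent samples. The section therefore gives the same test two names and assigns it to two different tasks. For the within-group task it does not fit: baseline and week 8 come from the same child, and the test treats them as if they came from different children. A statistician who followed the text would fail to detect real changes over time. The Objectives section states as a hypothesis that the therapy improves vision, so within-group results are likely to be reported and read.

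Between arms the issue is efficiency. Both primary outcomes are measured at baseline, but the named tests have no place for the baseline value as a covariate. With 62 children, precision that costs nothing is worth taking.

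**Working it through.** **Inputs from the article.** Effect size 0.8; two-sided alpha 0.05; power 80%; 26 evaluable children per arm (Sample Size); four measurement rounds; 4 hospitals.

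**Assumptions, not in the article.** Baseline-to-follow-up correlation rho, shown over a range; a within-group shift of 0.3 SD and a between-group difference of 0.5 SD, both for illustration; a between-hospital share of variance (ICC) of 0.05 to 0.20; normally distributed values with equal variances.

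**1. The plan's own figure.** By the normal approximation, n per arm = 2(1.960 + 0.842)² / 0.8² = 24.5, so 25. The exact t calculation gives 25.5, so 26 per arm and 52 in total, with power 0.807. The stated 52 is reproduced as an unadjusted two-sample t test.

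**2. The two rank tests are one.** On one simulated data set, the rank sum and Mann-Whitney tests gave the same p value, 0.22709.

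**3. Rank sum on paired data.** The variance of a mean before-after difference is 2σ²(1 − rho)/n. A test for independent samples works as if it were 2σ²/n, so it overstates the variance by about 1/(1 − rho): 2-fold at rho 0.5 and 5-fold at 0.8. Simulation with 10,000 runs of 26 pairs:

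| rho | Type I error, rank sum | Type I error, signed-rank | Power at 0.3 SD, rank sum | Power at 0.3 SD, signed-rank |
|---|---|---|---|---|
| 0.3 | 2.1% | 4.7% | 13% | 23% |
| 0.5 | 0.6% | 4.6% | 10% | 30% |
| 0.7 | 0.1% | 5.2% | 6% | 45% |
| 0.8 | 0.02% | 4.8% | 4% | 62% |

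**4. Between arms.** With 26 per arm, the SE in SD units is √(2/26) = 0.277 for follow-up values alone. Multiply the variance by 2(1 − rho) for change scores and by 1 − rho² for ANCOVA. The ratio of ANCOVA to change score is (1 − rho²)/(2(1 − rho)) = (1 + rho)/2.

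| rho | SE follow-up | SE change | SE ANCOVA | ANCOVA variance / follow-up | ANCOVA variance / change |
|---|---|---|---|---|---|
| 0.5 | 0.277 | 0.277 | 0.240 | 0.75 | 0.75 |
| 0.7 | 0.277 | 0.215 | 0.198 | 0.51 | 0.85 |
| 0.8 | 0.277 | 0.175 | 0.166 | 0.36 | 0.90 |

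Power at a difference of 0.5 SD is 42% for follow-up values alone. At rho 0.5, 0.7 and 0.8 it is 42%, 63% and 80% for change scores, and 53%, 70% and 84% for ANCOVA.

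**5. Hospital.** Simulation with 4,000 runs and 4 hospitals of 13 children. If allocation is balanced within hospital, the unadjusted t test has a type I error of 4.7%, 4.3% and 3.6% at ICC 0.05, 0.10 and 0.20. Under simple randomisation it is about 5%. Leaving hospital out did not inflate the error in either case.

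**The case against.** The within-group wording may be a slip for signed-rank, since the section presents the two rank tests as different tests. The t test, as named, could be a paired one. The error yields missed findings rather than false ones, and within-group tests do not decide a noninferiority question between arms. All of this stands and limits the consequence. It does not make the named test right.

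A reader might go further and infer that the between-group analysis ignores baseline, that its standard errors are wrong, and that adjustment would be worth 2.8 times the sample size (1/0.36 at rho 0.8). The article does not support this.

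- It does not say that follow-up values alone are compared. The UCVA criteria count lines of improvement, and Expected Findings speaks of improvements, so change scores are a live reading. Against change scores the factor at rho 0.8 is 1/0.90 = 1.11.
- The unadjusted tests hold their type I error at or below nominal. They are less precise, not invalid.
- The correlation is assumed throughout.
- Covariates may be set out in an analysis plan that is not shown, so their absence here is not an error.

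The practitioner sentence might also be read as a fixed rule for choosing the model from the data. It is a tentative remark among the limitations, and it concerns neither baseline nor hospital.

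**Conclusion.** The within-group test is wrong as written. At any positive correlation it is conservative and loses power; how much depends on rho, which the article does not give. The practical weight is modest, because the trial's conclusion rests on the comparison between arms.

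Baseline-adjusted ANCOVA is a recommended improvement, not the correction of an error. Under the normal model used here, its large-sample variance is never above that of either unadjusted alternative. The gain runs from small to large according to rho and to whether change or follow-up values are meant. Adding hospital brings little.

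**What to change.** - In Data Analysis, name the Wilcoxon signed-rank test for within-group comparisons of non-normal data and the paired t test for normal data, and label both as descriptive.
- For each primary outcome, replace the plain between-group t or Mann-Whitney test with ANCOVA on arm and the baseline value of that outcome. Report the adjusted difference with its 95% CI. A hospital term is optional.
- State in advance whether a practitioner term enters the model, or confine it to a sensitivity analysis.

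The cost is wording in the protocol and analysis plan, plus one degree of freedom for baseline and three more if the 4 hospitals are included. No new data are needed. Recruitment is planned to run to October 2026, so there is time. The Results section already describes how outcomes look under tuina with 29 children enrolled, so the change should be dated and made before any further look at the data.

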## Discussion

### Expected Findings

This study aims to evaluate the efficacy and safety of *tuina* therapy through a randomized controlled clinical trial. We anticipate that children who receive *tuina* therapy will show improvements in AL, UCVA, SE, and AMP that are not inferior to those achieved through drug therapy. Furthermore, we expect that *tuina* therapy will be safer, free of adverse effects, and exhibit more stable long-term efficacy.

The high prevalence and severe complications of myopia have inflicted significant damage on the visual health of adolescents, imposing a substantial burden on both society and the economy. Therefore, the urgent need for an effective method to prevent and control myopia is evident. *Tuina* is a potential alternative therapy for myopia. However, current research on the application of *tuina* therapy for myopia predominantly focuses on local ocular areas, neglecting the holistic perspective, which to some extent limits its therapeutic efficacy. The holistic perspective is a fundamental concept in TCM, which views the human body as an integrated whole. This perspective posits that the human body is a harmonious entity, with the heart as the master and the 5 organs at the center, interconnected through the meridian system. This holistic entity is indivisible in terms of structural integration, functionally coordinated, and pathologically interrelated. Consequently, in the rehabilitation of myopia, it is imperative not only to address local symptoms around the eyes but also to promote the overall regulation of the child’s body.

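### The trial is declared noninferiority, but its sample size and stated tests are for a difference; unless tuina proves significantly better, they cannot establish noninferiority

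*Protocol article*

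**What the plan says.** Three places in the protocol article commit to noninferiority:

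- Study Design: "This study is designed as a multicenter randomized controlled noninferiority trial".
- Abstract, Conclusions: the hypothesis is that the effect of tuina "therapy is noninferior to that of tropicamide eye drops".
- Discussion, Expected Findings: improvements in axial length, uncorrected visual acuity (UCVA), spherical equivalent and accommodative amplitude "that are not inferior to those achieved through drug therapy".

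Two places fix the statistics, and both describe a difference test:

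- Sample Size: "To detect between-group differences with 80% statistical power" and "we choose a 2-tailed α level of .05", with an effect size of 0.8. This gives 26 per group (52), raised to 62 for 20% dropout.
- Data Analysis: a t test, or for nonnormal data the Mann-Whitney "test for between-group comparisons". A two-sided P "value of .05 will be considered statistically significant". No other criterion for a conclusion is given.

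The Objectives section states a further hypothesis (better vision, greater safety than the drug, more stable long-term effect) that does not mention noninferiority. UCVA and axial length are both listed as primary.

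**The concern.** A noninferiority conclusion needs evidence that tuina is not worse than tropicamide by more than a stated amount. A test of no difference does not supply this when the arms turn out similar, which is the situation a noninferiority design anticipates. The result is then P>.05, which means only that zero has not been excluded. A real deficit may be equally compatible with the data.

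Two things are at stake. The headline conclusion could rest on a non-significant P value, a result that becomes more likely as the trial gets smaller, noisier or less complete. The 80% power also belongs to a question other than the one the trial says it asks.

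**Working it through.** **Inputs.** From Sample Size: two-sided alpha .05, power 80%, effect size 0.8 (read as a standardised mean difference), 1:1 allocation, 26 per group, 62 in total, 20% dropout. The article gives neither a margin nor an SD, so every margin and true deficit below is an assumption in SD units.

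**1. Reproduce the plan's figure.** For a two-sided two-sample t test with n per arm, df = 2n − 2 and noncentrality = d × √(n/2).

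- n = 25: noncentrality 0.8 × √12.5 = 2.828, power 0.791.
- n = 26: noncentrality 0.8 × √13 = 2.884, critical t (50 df) 2.009, power 0.807.

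The smallest n reaching 80% is 26 per arm, or 52 in total, exactly as stated. The calculation is therefore a two-sided test for a difference.

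**2. How often does that test give P>.05 when tuina is truly worse?** (26 per arm, noncentral t)

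| True deficit | Noncentrality | Probability of P>.05 |
|---|---|---|
| 0.2 SD | 0.721 | 0.89 |
| 0.3 SD | 1.082 | 0.81 |
| 0.5 SD | 1.803 | 0.58 |
| 0.8 SD | 2.884 | 0.19 |

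With all 31 per arm analysed, the 0.3 and 0.5 SD figures are 0.79 and 0.51, so full retention does not rescue the rule.

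**3. Precision.** The half-width of the 95% CI at 26 per arm is 2.009 × √(2/26) = 0.56 SD. A non-significant result with an estimate near zero still allows a deficit of about half an SD.

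**4. Power for the declared objective.** Test at one-sided .025 with true difference 0. Noncentrality = margin × √(n/2), 26 per arm.

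| Assumed margin | Power |
|---|---|
| 0.3 SD | 0.18 |
| 0.5 SD | 0.42 |
| 0.79 SD | 0.80 |

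**5. Margin supported after dropout.** 62 × 0.8 = 49.6, about 50 evaluable or 25 per arm. Solving for 80% power gives a margin of about 0.81 SD.

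**6. Size needed for a narrower margin.** By the normal approximation, n per arm = 2 × (1.96 + 0.8416)² / margin². A margin of 0.5 SD gives 62.8, so 63 per arm and 126 before dropout (126/0.8 = 157.5, so 158 enrolled). A margin of 0.3 SD gives 174.4, so 175 per arm and 350 before dropout.

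**The case against.** **The rule is not useless.** A result significantly in favour of tuina excludes zero and every worse value, and so implies noninferiority at any positive margin. A reader might infer that the trial can reach its conclusion only by misreading P>.05, or that no result could support it. Neither follows. This objection stands, and it limits the point to results that are not significantly better.

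**The margin may be elsewhere.** This is a condensed article, and a full protocol or SAP may contain a margin, a confidence-interval rule and analysis sets. That is fair, and their absence here is not the finding. The finding is that the article does fix a sample size and a test criterion, and both belong to a difference question. An unseen SAP could add a margin, but it would not turn the printed sample-size calculation into a noninferiority calculation.

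**Two-sided .05 is not wrong in itself.** It matches a two-sided 95% CI, which is the usual basis for a noninferiority decision. This also stands: the alpha level is acceptable. The problem is using it to test for a difference.

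**Intent.** A reader might infer that the sponsor means to present P>.05 as proof of noninferiority. The article does not say so. It simply offers no other route when the arms are similar.

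**Conclusion.** The contradiction is real and needs correcting before analysis. The article declares noninferiority, sizes the trial to detect a difference of 0.8 SD, and states only difference tests. Unless tuina is significantly better, these rules cannot establish what the trial sets out to show, and the 80% power does not describe the declared objective. It would do so only for a margin near 0.8 SD, which the article neither states nor justifies.

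The figures assume a continuous outcome, equal variances, equal arms and, for noninferiority power, no true difference. The margins are illustrative, but the contradiction does not depend on which one is chosen.

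**What to change.** Amend the Sample Size and Data Analysis sections.

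1. **Decision rule.** Conclude noninferiority only if the relevant bound of the two-sided 95% CI for tuina minus tropicamide lies inside the margin, in both the full-analysis and per-protocol sets.
2. **Outcomes.** Set a margin for each primary outcome (UCVA in logMAR, axial length in mm), or give one of them a stated lesser role. Name one time point.
3. **Source of the margin.** Justify it from external evidence on the control effect, not from what 62 children can support. As of December 2025, 29 children were enrolled, and the Results section already describes the accrued UCVA and axial-length data as favouring tuina. The margin should therefore be set by people without access to those outcomes, and the amendment should be openly dated.
4. **Power.** Restate the power of 62 children for that margin, using about 50 evaluable.
5. **Fallback.** If no margin as wide as about 0.8 SD can be defended, remove the noninferiority claim from the Abstract, Study Design and Expected Findings. Report the estimated difference with its 95% CI, and do not read P>.05 as evidence of noninferiority.
6. **Consistency.** Bring the hypothesis in Objectives into line with whichever framework is kept.

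The cost is an amendment to the wording and a less favourable claim. No extra children are needed if a margin near 0.8 SD is defensible or the noninferiority claim is dropped. Keeping 80% power for a narrower margin would mean a much larger trial, for example 126 evaluable children at 0.5 SD.
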